## Abstract

**Background::**

Postoperative gastrointestinal dysfunction (PGD) refers to one of the common postoperative complications. Acupuncture can facilitate the recovery of PGD, whereas no therapeutic schedule of acupuncture has been internationally recognized for treating PGD. In the present study, a scientific trial protocol has been proposed to verify the feasibility of acupuncture in treating gastrointestinal dysfunction after laparoscopic cholecystectomy under general anesthesia. We conduct this protocol to investigate whether acupuncture recovery gastrointestinal dysfunction by influencing the expression of gastrointestinal hormone.

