### Intervention

2.10

The treatment strategy of this study will be collectively formulated by experienced acupuncturists, surgeons and anesthesiologists. After laparoscopy, all the subjects will be fasted and in supine position without pillow, the intervention is going to be conducted once 30 min after surgery. The experimental group will receive the treatment of sterile disposable stainless-steel needles (*Huatuo* medical instruments Co. Ltd., Suzhou, China; 0.3 mm × 40 mm/0.3 mm × 25 mm). Acupoints will be located abiding by the World Health Organization Standard Acupuncture Point Locations in the Western Pacific Region.^[32]^ The fixed prescription includes *Hegu* (LI4), *Neiguan* (PC6), *Zusanli* (ST36), *Gongsun* (SP4), lateral line 2 of forehead (MS3), lateral line 3 of forehead (MS4), and middle line of vertex (MS5) (Fig. 3), all acupoints will be bilaterally selected except for middle line of vertex (MS5). The acupuncture needles will be inserted into acupoints after the routine sterilization; subsequently, it will be evenly lifted, inserted and then twisted to *Deqi* after reaching the standard depth; the operation of each acupoint will take 30 s. The needles will be maintained on the trunk and limbs for 30 min and on the head for 6 h after *Deqi*. Acupuncture will be performed by two acupuncturists registered in China and with over 3 years of clinical experience. They will receive the relevant training before the experiment, the training courses covered acupoint positioning, acupuncture operation skills and communication skills. The control group will be intervened by professional surgical nurses, the treatment will be intravenous injection of granisetron with 3 mg/3 mL (drug approval No. H20030161, Sichuan Taiji Pharmaceutical Co., Ltd).

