#### Secondary outcome

2.11.3

1.Time to first defecation: Researchers will inform the subjects and their families to assist in recording the interval between the time of subjects returning to the ward after the operation to the time of first defecation after operation.2.Abdominal pain: The Visual Analog Scale (VAS, Fig. 4) will be adopted to assess the degree of postoperative abdominal pain of subjects,^[27]^ which is to be recorded by researchers at t_1_ to t_5_.3.Dosage of analgesia pump: Considering that the use of analgesia pump will affect the degree of abdominal pain,^[33]^ therefore, the dosage of analgesia pump used by participants after operation will be recorded by researchers at t_1_ to t_5_.4.Abdominal distention: Likert scale (see Table 2) will be adopted to assess the degree of abdominal distention^[30,34]^ and recorded by researchers at t_1_ to t_5_.5.Nausea: The VAS scale will be employed to assess the degree of nausea^[27]^ and recorded by researchers at t_1_ to t_5_.6.Vomiting: The subjects and their families will help record the times of vomiting at t_1_ to t_5_.7.Gastrointestinal hormones: Blood samples will be taken 8 h before operation, 30 min after operation, and 24 h after operation to detect the level of gastrointestinal hormones. Enzyme-linked immunosorbent assay will be used to detect the levels of serum gastrin, motilin, ghrelin, 5-HT in the two groups. Three milliliters of blood will be harvested from the vein in the fasting state. The blood samples will be kept at ambient temperature for 30 min and then centrifuged at 3500 rpm for 10 min; the serum will be stored in a refrigerator at −70°C for testing. Serum samples will be collected by clinical centers, and relevant tests will be performed by Chengdu Lilai Biotechnology Co., Ltd.8.Psychological status: The Hospital Anxiety and Depression Scale (HADS) will be adopted to assess the psychological status of the subjects at t_0_ and t_6_.^[35]^ HADS has two subscales of anxiety and depression. There will be seven problems for anxiety and depression respectively. The anxiety and depression are expressed by the score of 0 to 7 points (no symptoms), 8 to 10 points (suspicious symptoms), 11 to 21 points (obvious symptoms). The first evaluation will be conducted 8 h before the operation, and the second one will be conducted on the day of discharge.

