#### Sample size calculation

2.15.1

The total sample size of the study will be calculated by the formula based on a two-group, parallel, controlled design: n = (*Z*_1−*α*/2_ + *Z*_1−*β*/2_)^2^ × (*σ*2 1 + *σ2 2*)/*δ*^2^, where n denotes the sample size of each group, *σ* represents the standard deviation, and δ indicates the clinical significance between groups. At an α = 0.05, power = 80%, and given a bilateral test, *Z* scores of *Z*_1−*α*/2_ = 1.96 and *Z*_1−*β*/2_ = 0.84 will be obtained from the *Z* score table. Eighteen subjects recruited from February 2018 to March 2018 will be recruited in the pilot trial, and the primary outcome measure will be the time to first flatus: S1 = 2.21 and S2 = 3.53. Based on preliminary trial and clinical experience, the reduction of 4 h in the time to first flatus will be defined as our clinical expectation. Accordingly, the rounded sample size in each group is n ≈78. Assuming that the dropout rate is 15%, 180 subjects (90 in each group) will be needed in the two groups.

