#### Statistical analysis

2.15.2

1.Analysis procedures sample distribution: The number of dropouts and the rate will be described and analyzed for each data set, and the reasons for any dropouts are elucidated.2.Balance comparison: The subjects’ general data will be compared to assess the comparability of the two groups.3.Efficacy analysis: The subjects’ time to first flatus will be used as the primary outcome measure to assess the efficacy and safety of acupuncture in treating PGD. The means (χ) and standard (SD) deviations will be calculated to express the outcome measure, and the experimental and control groups will be statistically compared by two independent-sample *t* tests. Eight secondary outcomes will be applied to assess the efficacy of the acupuncture. Seven of these—namely, time to first defecation, abdominal pain, dosages of analgesia pump, abdominal distention, nausea, vomiting, and gastrointestinal hormones will be described usinḡχ± SD deviation and statistically compared between groups by Repeated Measures Analysis of Variance (RMANOVA). The statistical analysis of time to first defecation will be identical to that of time to first flatus. However, before performing RMANOVA, a sphericity test will be performed to determine whether the data are suitable for analysis by RMANOVA. If the data do not conform to the conditions of sphericity condition, the degree of freedom will be corrected using factor ε before the RMANOVA is performed. The categorical measure of psychological status will be analyzed using either the rank-sum test or Spearman's rank correlation.4.Safety analysis: In accordance with the definition of adverse events, specific adverse events, their severity level, causes, and explanations will be listed. The number of adverse events, and the incidence of adverse event will be statistically described. If inter group comparison is required, the χ^2^ test or Fisher's exact test will be performed.5.Methods of statistical analysis: An independent statistician analyzed the outcome data in accordance with the principle of intention-to-treat (ITT), that is, all subjects recruited in the group will be covered. The analysis of efficacy and safety indicators will be conducted following the principle of per-protocol (PP), that is, all subjects who completed the whole trial process without major protocol violations will be included. All statistical analysis complied with ITT population, and the results of ITT analysis will be compared with PP analysis to assess the sensitivity. All missing data will be analyzed using the last observation carried forward (LOCF) interpolation method. The qualitative data will be tested for normality, according to which independent *t* test or Mann–Whitney *U* test will be performed for groups comparison. Qualitative variables will be presented by the statistical description of χ ± SD of the normal distribution data, whereas qualitative variables will be recorded as the number of cases in each category. If the quantitative variables constitute repeated measures data, RMANOVA will be adopted for comparison, and the sphericity test will be performed to ascertain the applicability of, as well as to correct the data. The categorical variables will be represented by numbers (percentages) by χ^2^ test or Fisher's exact test *P* < .05 will be considered statistically significant on both sides in all the statistical tests. SPSS 25.0 software (SPSS, SPSS Inc, Chicago, IL) will be adopted for data statistical analysis.

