Given the theoretical research of acupuncture and long-term clinical experience, this study hypothesizes that acupuncture may promote the recovery of gastrointestinal dysfunction after laparoscopic cholecystectomy under general anesthesia by changing the level of gastrointestinal hormones. A systematic review^[35]^ revealed that the time to first flatus after operation is of high clinical implication in the recovery of gastrointestinal motility.^[39]^ In most clinical trials regarding PGD, the time to first flatus is considered as the primary result, so it acts as the main outcome index here. PGD can cause emotional impact on patient, so the anxiety and depression of the subjects act as the secondary observation indexes as well.^[40]^ In the inclusion criteria of this study, subjects aged from 18 to 70 will be selected to cover as wide a range as possible. In the meantime, exclusion of participants taking gastrointestinal motility related drugs is critical for accurate clinical results. During the study, patients will be allowed to use rescue drugs when having intolerable symptoms; this strategy reflects the clinical practice in the real world and meets the moral obligation.

This study has some limitations. To be specific, the drug control group was designed, instead of the placebo sham acupuncture control group. In the previous experiment, we found that even intradermal acupuncture or transcutaneous electrical stimulation can exert physiological effects, which might be attributed by the specificity of acupoints. At present, there has been an absence of internationally recognized criterion and mature method of sham acupuncture.^[41]^ Moreover, it is difficult to blind subjects since most of Chinese patients have received acupuncture before, so the trial lacked sham acupuncture control group. In brief, this study protocol described a randomized, evaluated blinded, multi-center clinical controlled trial. The results of this study will evidence the effectiveness, safety, and feasibility of acupuncture for gastrointestinal dysfunction after laparoscopy; the aim of this study is to provide reliable reference for facilitating the clinical application of this therapy.

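### Blanket LOCF fills a missing 24 h hormone value or discharge HADS score with a value from before or at the start of treatment, which biases the between-arm comparison of these outcomes

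*Protocol article*

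**What the plan says.** All references are to the protocol article.

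- **Missing data** (2.15.2 Statistical analysis, item 5): "All missing data will be analyzed using the last observation carried forward (LOCF) interpolation method". No outcome is exempted.
- **Treatment time** (2.10 Intervention): "the intervention is going to be conducted once 30 min after surgery".
- **Hormones** (2.11.3 Secondary outcome, item 7): "Blood samples will be taken 8 h before operation, 30 min after operation, and 24 h after operation". Gastrin, motilin, ghrelin and 5-HT are measured.
- **HADS** (2.11.3, item 8): "The first evaluation will be conducted 8 h before the operation, and the second one will be conducted on the day of discharge".
- **Tests** (2.15.2, item 3): hormones by RMANOVA with a sphericity correction; psychological status by a rank-sum test or Spearman correlation.
- **Analysis sets** (2.15.2, item 5): ITT is the main set, and its results are compared with a per-protocol (PP) analysis as the sensitivity check.
- **Role of the hormones**: the Abstract gives an aim "to investigate whether acupuncture recovery gastrointestinal dysfunction by influencing the expression of gastrointestinal hormone", and the Discussion hypothesises that acupuncture works "by changing the level of gastrointestinal hormones".
- **Dropout** (2.15.1 Sample size calculation): a 15% allowance, applied to the sample size for time to first flatus.

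**The concern.** LOCF is usually defended on the ground that an earlier on-treatment value is a tolerable stand-in for a later one. For these two outcomes there is no earlier on-treatment value. The 30 min hormone sample coincides with the start of treatment and the other early values precede surgery. A patient without a late value therefore enters the ITT comparison with an untreated value labelled as a post-treatment one, and the analysis counts it as a real observation.

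Two separate results are affected: the hormone comparison, which carries the trial's mechanism question, and the HADS comparison, which is a secondary outcome outside that question. If few late values are missing, little is lost. If many are missing, a real effect is diluted. If they are missing unevenly while patients in both arms change after surgery, a difference can appear, disappear or grow for reasons unrelated to treatment.

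**Working it through.** **1. Which value is carried.** Setting the schedule beside the treatment time:

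| Outcome | Before or at start of treatment | After treatment | LOCF value if the late one is missing |
|---|---|---|---|
| Hormones | 8 h pre-op; 30 min post-op | 24 h post-op | 30 min value, or the pre-op value if that is missing too |
| HADS | 8 h pre-op | day of discharge | pre-op score |

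**2. Expected bias.** Let τ be the true between-arm difference in the late value, c the control-arm change from the carried value to the late value, and pT and pC the missing shares in the acupuncture and control arms. Assume equal early means (randomisation) and missingness at random within arm. Then

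expected LOCF difference = (1 − pT)·τ − (pT − pC)·c.

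**3. Equal missingness, pT = pC = p.** The second term vanishes and (1 − p)·τ remains, whatever c is.
- p = 0.05: 0.95 τ.
- p = 0.15: 0.85 τ. A true 0.50 SD becomes 0.85 × 0.50 = 0.425 SD.

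Simulation (90 per arm, 4000 runs, assumed correlation 0.5, p = 0.15) gave 0.42 SD with LOCF and 0.50 SD from observed values. For a simple t test on the late value, power was 80% (no trend) or 73% (1 SD trend) with LOCF, against 86% with observed values. The t test only illustrates the loss; it is not the planned test for these outcomes.

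**4. Unequal missingness (assumed 20% v 10%, acupuncture v control).** The bias is −0.20·τ − 0.10·c.
- τ = 0, c from −1 to +1 SD: +0.10 to −0.10 SD.
- τ = 0.50 SD, c from −1 to +1 SD: estimates from 0.50 to 0.30 SD.

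With the shares reversed (10% v 20%), a true 0.50 SD is estimated at 0.35 to 0.55 SD.

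**5. Type I error of the planned tests.** No true effect, 90 per arm, correlation 0.5, 4000 runs, LOCF applied:

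| Missing, trend | RMANOVA group-by-time | RMANOVA between groups | Rank-sum |
|---|---|---|---|
| 20% v 10%, 1 SD | about 10% | about 6% | about 9% |
| 20% v 10%, 2 SD | about 21% | about 8% | about 17% |
| 17% v 13%, 1 SD | near 5% | near 5% | near 5% |

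RMANOVA on completers only stayed at about 5% under the same missingness at random.

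The 15% dropout is the only figure here that the protocol supplies. The effect sizes, trends, correlation and splits between arms are assumptions.

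**The case against.** Four points on the other side deserve weight.

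- **The 15% is not the missing rate at 24 h or discharge.** It is an overall allowance, and complications are recorded until two weeks after discharge. Values due during the hospital stay may be missing less often. This stands: 0.85 is a what-if, and at 5% missing the shrinkage is 5%.
- **Nothing shows unequal loss or a large common trend.** Also correct. Patients and acupuncturists are unblinded, so uneven loss is conceivable, but the protocol does not indicate it. A reader might infer that LOCF is likely to produce a false mechanism claim. The documents do not support that. Equal missingness pulls towards no effect, and at 17% v 13% with a 1 SD trend the planned tests keep their level. Nor should error rates from an ANCOVA (about 12% and 24% at 20% v 10% missing with 1 and 2 SD trends) be attributed to the plan, which does not use that test.
- **The PP comparison already helps.** For these outcomes it comes close to a completers' analysis and, with missingness at random within arm, holds the error rate. This stands in part. PP is secondary and also excludes protocol violators, so a gap between ITT and PP could not be attributed to LOCF, and the ITT result stays biased.
- **An article condenses its protocol.** That would excuse an omission. Here a rule is stated and covers everything.

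A reader might also take HADS as part of the mechanism question. The Abstract and Discussion name only the hormones there.

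**Conclusion.** The point holds, at modest size. The stated rule, read with the stated schedule, substitutes values from before or at the start of treatment for post-treatment values of hormones and HADS. The dilution to (1 − p) follows by arithmetic when missingness is equal and at random within arm; its size depends on a missing share that the protocol does not give. Bias in either direction, and any excess of false positives, needs both unequal missingness and a common postoperative change; neither is documented, and with a small imbalance the excess is negligible. The primary outcome plays no part in this point. The rule should be changed because it serves no purpose for these outcomes, bears on the trial's mechanism question and is cheap to replace.

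**What to change.** In item 5 of 2.15.2, remove LOCF for hormones and HADS, and state that a preoperative or 30 min value is never entered as a post-treatment outcome. Then:

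- **Hormones:** fit a likelihood-based mixed model to all observed sampling times, which keeps patients with partial data.
- **HADS:** analyse the observed discharge scores, preferably adjusted for the preoperative score.

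The cost is a change of wording and a little more analysis work, with no new data or patients. The small downside is that the analysis assumes values are missing at random; a multiple-imputation sensitivity analysis is optional. If the LOCF sentence is also revised for other outcomes, make it one edit.

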### Elimination standard

2.6

Subjects will be eliminated from the trial if meeting any of the following conditions:

1.laparoscopy must be converted to laparotomy;2.refusal to continuous treatment for various reasons;3.with severe syndromes (e.g., biliary fistula and peritonitis) during the treatment;4.transferred to other specialist treatments;5.having become comatose or die;6.cannot participate in the follow-up for various reasons;7.researchers accidentally included the subjects not meeting the inclusion criteria;8.less compliance with the treatment regulations and failed to provide information that might be critical to the evaluation.

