#### Primary outcome

2.11.2

Time to first flatus: the researcher will inform the subjects and their families to help record the interval between the time of subjects returning to the ward after the operation to the time of first flatus after operation.

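### LOCF cannot supply a missing time to first flatus or defecation, because each is measured once, and the plan gives two different rules for the primary test

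*Protocol article*

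**What the plan says.** All references are to the protocol article.

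- **Missing data (2.15.2, item 5).** "All missing data will be analyzed using the last observation carried forward (LOCF) interpolation method". No outcome is exempted.
- **Analysis set (2.15.2, item 5).** Intention to treat, meaning that "all subjects recruited in the group will be covered". A per-protocol analysis is added for comparison.
- **Primary outcome (2.11.2).** One interval per patient: "the interval between the time of subjects returning to the ward after the operation to the time of first flatus after operation". Time to first defecation (2.11.3) is defined in the same way.
- **Primary test, first statement (2.15.2, item 3).** Means and SDs are reported and "the experimental and control groups will be statistically compared by two independent-sample" t-tests, without condition. For the other time, "The statistical analysis of time to first defecation will be identical to that of time to first flatus".
- **Primary test, second statement (2.15.2, item 5).** "The qualitative data will be tested for normality, according to which independent" t-test or Mann-Whitney U is used. The primary outcome is not exempted here either.
- **Exits (2.6).** Conversion to laparotomy, refusal, severe complications, transfer, coma or death, and patients who "cannot participate in the follow-up for various reasons".
- **Dropout (2.15.1).** 15% is assumed, with 180 patients in total.

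**The concern.** LOCF needs an earlier measurement of the same quantity, and an elapsed time to a first event has none. For a patient who leaves before flatus, all that is known is that the time exceeds the last contact, and neither of the named tests uses that information as specified. The analyst would have to improvise, either dropping the patient, which departs from the stated intention-to-treat set, or inventing a value. The most natural misuse of LOCF here is to enter the time of last contact as if flatus had occurred then, which makes early leavers look like fast recoverers.

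The two test rules add a second choice made after the data are seen. A t-test compares means and Mann-Whitney compares ranks. Only a mean difference corresponds to the 4 h target on which the trial is sized.

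LOCF also fits the repeated outcomes poorly:
- It copies early postoperative pain and nausea scores into later windows.
- It copies vomiting counts and pump doses between windows of different length.
- It carries the hormone sample taken 30 min after surgery to 24 h.
- It carries the preoperative HADS score to discharge.

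**Working it through.** **1. How many patients could be affected.** Inputs: 15% dropout and N = 180 (2.15.1). 0.15 × 180 = 27. This is an upper bound, reached only if every dropout comes before flatus. The plan's step from 78 to 90 per group reproduces as 78 × 1.15 = 89.7. (The 78 does not follow from the plan's formula: 2.8² × (2.21² + 3.53²)/4² = 8.5. That is a separate matter and nothing here depends on it.)

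**2. When flatus is likely to have happened.** Inputs: pilot means and SDs (Introduction), 16.31 ± 2.21 h with acupuncture and 26.14 ± 3.53 h in controls. Normality is assumed, and the short gap between surgery and return to the ward is ignored.

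| Time | Controls without flatus | Acupuncture without flatus |
|---|---|---|
| 24 h | z = (24 − 26.14)/3.53 = −0.61; 73% | z = (24 − 16.31)/2.21 = 3.48; under 0.1% |
| 36 h | z = 2.79; 0.3% | z = 8.9; effectively none |
| 48 h | z = 6.19; effectively none | effectively none |

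The pilot had only 18 patients, so the control SD may be too small. An SD of about 8.9 h is what n = 78 would need at a 4 h difference (4 × √(78/2)/2.8 = 8.92). With that SD, 13% of controls would be without flatus at 36 h and 0.7% at 48 h. In both cases the end of observation censors very few patients. The risk comes from early exits.

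**3. Entering last contact as the event time.** Illustrative assumptions: control mean 26.14 h, pilot SDs, 90 per arm, and exits at a uniformly distributed fraction of the patient's own flatus time. Half the time is then lost on average, so each arm's mean is multiplied by (1 − dropout/2).

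- No true difference, 20% acupuncture and 10% control dropout: 26.14 × 0.95 − 26.14 × 0.90 = 1.3 h of spurious benefit. In a simulation of 4,000 trials the two-sided t-test rejected in about 29%.
- No true difference, 15% in each arm: no bias, and rejection at about 5%.
- True difference 4 h, 15% in each arm: 26.14 × 0.925 − 22.14 × 0.925 = 3.7 h.
- True difference 4 h, 20% acupuncture and 10% control: 26.14 × 0.95 − 22.14 × 0.90 = 4.9 h.
- True difference 4 h, 10% acupuncture and 20% control: 26.14 × 0.90 − 22.14 × 0.95 = 2.5 h.

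**4. Dropping the patients.** In the same simulation exits did not depend on recovery speed, and dropping the patients gave no bias. Bias arises when the loss depends on speed. Suppose 15% of each arm leaves at 24 h and the pilot figures are true. Then 0.15 × 0.73 = 11% of controls lose their value, all of them slow, and almost no acupuncture patient does. By the truncated normal, controls with flatus before 24 h average 21.83 h. The remaining control mean is (0.85 × 26.14 + 0.15 × 0.272 × 21.83)/(0.85 + 0.15 × 0.272) = 25.94 h. The shift is 0.2 h, small against 4 h.

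**5. Two test rules.** Item 5 speaks of qualitative data, but these cannot be tested for normality or compared by a t-test, so quantitative data must be meant. Time to first flatus is quantitative and falls under that sentence. Item 3 fixes the t-test for it, while item 5 makes the test conditional.

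**6. Unequal windows.** From the Figure 2 legend, t4 is 12–24 h (12 h long) and t5 is 24–48 h (24 h long). Carrying a t4 total into t5 gives carried/true = 12r₄/(24r₅) = 0.5 × r₄/r₅, where r is the hourly rate. At a constant rate the value is halved. If the rate itself halves, the carried value happens to be right, and if it falls further the carried value is too high. The size and direction depend on a rate the document does not give.

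**The case against.** The strongest reply is that the damage is probably limited. The 15% dropout is not tied to any time point, follow-up runs to two weeks after discharge, and the pilot suggests that most patients pass flatus within a day and a half. The t-test can be run for everyone with an observed time. The plan also promises to report dropouts with reasons and to compare intention-to-treat with per-protocol results. All of this stands, and it limits the size of the problem. None of it gives the LOCF rule a value to carry.

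On the test, one can argue that item 3, being specific to the primary outcome, overrides a general and garbled sentence in item 5. That is a reasonable reading, but the text does not say so, and item 5 makes no exception.

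A reader might also infer that the lack of a censoring rule is itself an error. It is not treated as one here: a condensed article may leave that rule to the analysis plan. The error is that the article does state a rule, for all missing data, and that rule cannot work for these two outcomes.

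**Conclusion.** The point holds. For time to first flatus and time to first defecation the stated missing-data rule is unworkable, and for any patient without the event it conflicts with the stated intention-to-treat set. Items 3 and 5 also need to be aligned on the primary test.

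The size is bounded but unknown: at most 27 of 180 patients, and probably fewer. The bias could be nil, about 0.2 h, or more than 1 h, depending on how the gap is filled and whether exits differ by arm or recovery speed. These figures rest on the illustrative assumptions in the working.

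Three stronger readings are tempting but not supported:
- **That the primary analysis cannot be produced at all.** It can, for patients with an observed time. The rule fails only for the others.
- **That the late-recovery tail is lost.** No figure in the document shows this.
- **That discharge censors patients.** Patients and families help to record the time, and nothing says that recording ends at discharge.

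The window problem concerns secondary outcomes only, and the halving requires a constant rate.

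**What to change.** 1. **Remove LOCF** for time to first flatus and time to first defecation.
2. **Name one primary analysis in advance.** For example, use a log-rank test with patients without flatus censored at last contact. Add a restricted mean difference with 95% CI at a stated horizon, such as 48 h, to keep the link to the 4 h target. Analyse first defecation on the same principle, with its own stated horizon.
3. **State how each exit in section 2.6 is treated in the analysis.** Conversion, severe complications and death are plausibly informative, so simple censoring is doubtful for them. Add a sensitivity analysis that ranks these patients as worst outcomes.
4. **Keep the t-test on observed times** as a sensitivity analysis, and drop the normality gate for the primary outcome.
5. **Repeated outcomes.** Replace LOCF with a likelihood-based mixed model for VAS pain, VAS nausea, pump dose and hormones. Use a count model for vomiting and an ordinal model for distention. Account for window length where totals are analysed.
6. **HADS.** Do not carry the baseline value forward to discharge.

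Cost: mainly a change of wording before the data are unblinded. The primary result is no longer a plain mean difference, and the case report form must record the time of last contact without flatus, which the article does not show is collected.

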**Figure 2 F2:**
[figure not shown]
SPIRIT schedule of schedule of enrollment, interventions, and assessments. t1 is the day before surgery, t0 is the day of the surgery, t1 is 0 to 2 h after surgery, t2 is 2 to 6 h after surgery, t3 is 6 to 12 h after surgery, t4 is 12 to 24 h after surgery, t5 is 24 to 48 h after surgery, t6 is the day of the discharged, t7 is 2 weeks after patients discharged from the hospital.

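### LOCF on the t1–t5 pain, nausea and distention scores misstates late symptom levels if scores change during recovery, and can create a false group or group-by-time difference if losses differ by arm

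*Protocol article*

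**What the plan says.** **Missing data.** Statistical analysis (2.15.2), item 5: "All missing data will be analyzed using the last observation carried forward (LOCF) interpolation method". No outcome is exempted.

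**The scores.** Secondary outcome (2.11.3) has abdominal pain on a visual analogue scale, "which is to be recorded by researchers at t_1_ to t_5". For nausea, "The VAS scale will be employed to assess the degree of nausea", and for distention, "Likert scale (see Table 2) will be adopted to assess the degree of abdominal distention"; both are recorded over the same windows.

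**The windows.** The Figure 2 legend gives "t1 is 0 to 2 h after surgery, t2 is 2 to 6 h after surgery" and, for the last, "t5 is 24 to 48 h after surgery".

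**The comparison.** Item 5 of 2.15.2: "If the quantitative variables constitute repeated measures data, RMANOVA will be adopted for comparison", with a correction to the degrees of freedom if sphericity fails. Intention-to-treat (ITT) is the governing population. A per-protocol (PP) analysis is set beside it as the sensitivity check. Item 1 adds that dropout numbers, rates and reasons will be described.

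**Sources of loss.** Elimination standard (2.6) includes "refusal to continuous treatment for various reasons" and failure to take part in follow-up. Sample size calculation (2.15.1) assumes 15% dropout, not split by arm or by time.

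**The concern.** LOCF is unbiased for a mean only if the mean would have stayed flat after the patient left. These three scores describe how the patient feels at the time, during the first 48 h after an operation, and the hypothesis in the Discussion is that acupuncture speeds recovery. A flat course is hard to defend under that premise. A patient lost after t2 would carry the 2–6 h score into t3, t4 and t5, and the ANOVA would treat the three copied values as observations.

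Two things follow if the scores do change. Late symptom levels are wrong in both arms, whatever the pattern of loss. And if one arm loses more patients or loses them earlier, the arms diverge even with no treatment effect. Unequal loss is possible here: patients know their treatment (Blinding, 2.8), and one arm keeps head needles for 6 h while the other has one injection (Intervention, 2.10). The plan uses these outcomes to judge efficacy. The method is fixed in the protocol, so it is not a detail left for an analysis plan to choose.

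**Working it through.** The protocol gives no figure for the LOCF analysis, so there is none to reproduce. The check is how far LOCF departs from the truth when the two arms are identical.

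**From the protocol:** 90 per arm; 15% dropout (2.15.1); five windows (Figure 2 legend); two-sided 5% level (2.15.2).

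**Assumed, because the protocol does not give them:** score SD 2; within-patient correlation 0.5; last observation at t2; loss unrelated to the scores; mean falling evenly either 5, 4, 3, 2, 1 or 3, 2.5, 2, 1.5, 1 over t1–t5; no true group difference.

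**Step 1, bias at t5.** With loss rates p1 and p2 and last observation at t2:

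false difference = (p1 − p2) × (mean at t2 − mean at t5).

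- Fall 5 to 1, 20% v 10%: 0.10 × (4 − 1) = 0.30 points.
- Fall 5 to 1, 25% v 5%: 0.20 × 3 = 0.60 points.
- Fall 3 to 1, 20% v 10%: 0.10 × (2.5 − 1) = 0.15 points.
- Fall 5 to 1, 8% v 2%: 0.06 × 3 = 0.18 points.
- Fall 5 to 1, 6.7% v 3.3%: 0.034 × 3 = 0.10 points.
- Fall 5 to 1, 15% in each arm: no false difference, but both t5 means are too high by 0.15 × 3 = 0.45 points.

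**Step 2, rejection rates of the planned tests.** Null trials were simulated (3,000 to 4,000 per case), LOCF applied, and the ANOVA group test and the epsilon-corrected group-by-time test carried out. Nominal rate 5%.

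| Mean, t1 to t5 | Loss by arm | False difference at t5 | Group test | Group-by-time test |
|---|---|---|---|---|
| 5 to 1 | 20% v 10% | 0.30 | about 7% | 13–14% |
| 5 to 1 | 25% v 5% | 0.60 | 16% | about 45% |
| 3 to 1 | 20% v 10% | 0.15 | 6–7% | 6–7% |
| 5 to 1 | 8% v 2% (average 5%) | 0.18 | 5.5% | 7.7% |
| 5 to 1 | 6.7% v 3.3% (average 5%) | 0.10 | 4.9% | 6.2% |
| 5 to 1 | 15% v 15% | 0 | about 5% | about 5% |

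Simulation error on a 7% rate with 4,000 trials is about ±1.96 × √(0.07 × 0.93 / 4,000) = ±0.8 percentage points.

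**Step 3, other assumptions.** With SD 1.5, a fall of 5 to 1 or 4 to 2, and the last observation at t1 or spread over t1–t3, group-by-time rejection was 9–26% at 20% v 10% and 21–78% at 25% v 5%. With a flat course all tests stayed at about 4–7%, whatever the split.

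**Step 4, the alternative.** Generalised least squares on the observed scores only showed no bias and 4.7–5.4% rejection in the equal-loss, 20% v 10% and 25% v 5% cases. It used the true covariance, normal scores and loss unrelated to them, so it approximates a fitted mixed model but does not test one, and it does not test an ordinal Likert score.

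**The case against.** **The size is assumed.** The protocol gives no trajectory, score SD, correlation or loss by arm. Every patient has an analgesia pump and enhanced-recovery care, and rescue drugs are allowed, so a flatter course is plausible. This stands: the bias has a range that reaches down to nothing.

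**The 15% is not a 48 h figure.** A reader might infer that all of the planned dropout falls between t2 and t5. The documents do not support that. The 15% covers a trial that runs to 2 weeks after discharge, and missing follow-up is itself a ground for elimination. Other grounds, such as conversion to laparotomy or mistaken inclusion, may leave no score to carry. The scores come from inpatients and are recorded by researchers. This stands too, and the rows with 5% average loss may be nearer the truth.

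**Unequal loss is conjecture.** Treatment is given once, and the head needles come out about 6.5 h after surgery (30 min plus 6 h). After that neither arm has study treatment left to refuse. No section predicts a split. This stands, but refusal during those hours is exactly what would freeze a patient at an early score.

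**The ITT/PP comparison is a safeguard.** When loss is unrelated to the scores, an ANOVA of completers rejects at close to 5% even at 25% v 5%, so an LOCF artefact may show as a disagreement between the two analyses. This stands in part. The comparison does not correct the ITT result, which leads, and PP is itself unreliable if leaving depends on symptoms.

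**Conclusion.** The point holds as a conditional one. The protocol fixes LOCF for three scores that are likely to change over the 48 h in which they are measured. If they do change, late levels are misstated in both arms, even with equal losses. A false group or group-by-time difference arises only if the arms also differ in the amount or timing of loss.

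The size runs from negligible (equal loss, flat course, or about 5% average loss within 48 h, with rejection about 5–8%) to material (all 15% lost after t2 with a steep fall: group-by-time rejection 13–14% at 20% v 10% and about 45% at 25% v 5%). All of this rests on the assumed SD, correlation, trajectory and loss pattern.

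A reader might go further and infer that LOCF will produce a false difference in this trial. The documents do not show that, because they establish neither unequal loss nor a trajectory. Nor should inflated rejection in a separate test at t5 be counted: the plan compares these scores by repeated measures ANOVA and contains no such test. The point concerns three of eight secondary outcomes and does not bear on the primary one. The change is still worth making, since a better analysis is available at little cost.

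**What to change.** In 2.15.2, for pain, nausea and distention, replace LOCF followed by repeated measures ANOVA in the ITT analysis with a linear mixed model on all observed t1–t5 scores. Include group, window and group-by-window as fixed effects, with an unstructured covariance across windows (the MIXED procedure in SPSS 25) and no imputation. Report the group and group-by-window tests, which are the two the ANOVA was meant to give. Limit the LOCF sentence so that it no longer covers these scores in the main analysis, and retain LOCF for them only as a labelled sensitivity analysis.

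The cost is a wording change and slightly more analysis work in software the protocol already names. No extra data are needed. The small downside is that the mixed model relies on data being missing at random given the observed scores.
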